### 2.2. Sample Size Calculation

The primary analysis (see below) will focus on total severity of APS as evaluated using the Comprehensive Assessment of At-Risk Mental State (CAARMS) [1], measured in three longitudinal assessments (i.e., Feasibility phase: Baseline, T1, and T2). Accepting a type-I error (α) of 5% and a type-II error (β) of 20%, we would need a sample of 8–12 participants to detect an effect of large size (partial-η2 ≥ 0.140). This value was obtained considering a moderate-to-large test-retest reliability of measurements over time (+0.500 < r ≤ +0.700) and the absence of correction for sphericity. With an intermediate sphericity correction (ε = 0.750), the required sample size would be 10–14; in the worst case (ε = 0.500), instead, 12–19 participants would be needed. We therefore propose the recruitment of 20 participants, considered coherent with a pilot study and sufficient to evaluate feasibility outcomes of clinically significant size, also considering a low drop-out rate (i.e., ≤ 20%). When large statistically significant results are obtained on total severity of APS, specific APS severities will be further investigated (i.e., considering four P1 scales). For this secondary endpoint, on average, a sample-size of 17 participants would be sufficient to detect large effects, also considering Bonferroni’s correction for multiple independent comparisons (i.e., α = 0.012). Power analyses were carried out with G*Power-3.1.9.7 [45].

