### 2.8. Statistical Methods

#### 2.8.1. Data Verification, Statistical Monitoring, and Analysis

At the study start, a structured data verification plan will be agreed and developed by the Head Statistician ([name]) of the research team. Quality of data will be routinely checked in terms of consistency across paper- and electronic-based entry systems. Statistical monitoring will include patient severity level, eventual withdrawals, baseline data, FUP visits data, and adverse effects. The research team will approve a Statistical Analysis Plan within the early stages of the study, and before the Head Statistician summarizes any data (i.e., with univariate and repeated measures analysis, including preliminary assessment and management of any outliers and assessment of the metric qualities of measurements, such as normality and sphericity, where necessary). Proportions will be presented for each feasibility outcome. Interim analyses are not planned. The Head Statistician will both carry out and interpret statistical analysis. Our primary analysis will involve a generalized linear model with CAARMS psychotic symptom severity as the dependent measure and time as a repeated measure (possibly supplemented with analyses at the participant level, as random effects in mixed models). We are interested in whether there is a significant benefit over time with um-PEA treatment: therefore, particular interest will be placed on time as a fixed factor on the severity of outcomes. CAARMS distress and total score as well as HADS and GF ratings will be analysed in a similar manner. We will also conduct paired tests (both parametric and non-parametric) based on baseline and endpoint assessments to examine measures of CAARMS severity, CAARMS frequency/duration, and secondary outcomes. Trend and rates of adverse effects will be reported, as well as reasons for dropouts from the trial.

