#### 2.8.2. Missing Data

We expect withdrawn patients to be missing at random, and very few participants withdrawing consent. All patients having at least one post-baseline outcome measure will be included in each analysis. Nonetheless, patterns of missing data will be explored to investigate any evidence against missing at random, whose impact on the analysis will be considered by introducing imputation methods (i.e., Multiple Imputation or MissForest approach, depending on the missing data type).

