### 2.9. Withdrawal of Participants

In accordance with the Declaration of Helsinki [55], all participants have the right to withdraw from the study at any time, without the need to provide a reason, and without affecting their future medical care. Participants will be informed of this right prior to giving consent. If a participant decides to withdraw, it will be clarified that they are only discontinuing the study treatment while continuing follow-up visits. Should a participant wish to fully withdraw from the study, their decision will be respected. Efforts will be made to determine the reason for withdrawal, although participants are not required to provide any explanation. Data already collected will be retained and included in the final analysis. The PI may also withdraw participants for various reasons, including but not limited to protocol violations, intercurrent illness, adverse events, serious adverse events, suspected unexpected serious adverse reactions, administrative reasons, or if participation in the trial interferes with ongoing care or results in symptomatic worsening.

In these cases, participants will continue to be followed up with the same schedule of research assessments as those who remain in the study, until they complete the 12-week follow-up period or until they develop frank psychosis, whichever occurs first. Participants who experience progression to first-episode psychosis will exit the study intervention, be classified as treatment failure, and only be assessed for safety outcomes until completing the 12-week follow-up period.

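### Section 2.8.2 looks for evidence against missing at random in patterns that can speak only against missing completely at random, and answers it with methods that themselves assume missing at random

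*Protocol article*

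**What the plan says.** Section 2.8.2 of the protocol article starts from an assumption: "We expect withdrawn patients to be missing at random, and very few participants withdrawing consent". The analysis set follows: "All patients having at least one post-baseline outcome measure will be included in each analysis". The section then says that "patterns of missing data will be explored to investigate any evidence against missing at random", and continues: "whose impact on the analysis will be considered by introducing imputation methods (i.e., Multiple Imputation or MissForest approach, depending on the missing data type". It names no test, variable or threshold for the exploration, and no analysis that allows data to be MNAR.

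Three other places bear on this.

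- Section 2.2 sizes the primary analysis on total CAARMS severity, "measured in three longitudinal assessments (i.e., Feasibility phase: Baseline, T1, and T2".
- Section 2.8.1 makes the primary model a generalized linear model with time as a repeated measure, "possibly supplemented with analyses at the participant level, as random effects in mixed models". It adds paired baseline-to-endpoint tests, and says that reasons for drop-out will be reported.
- Section 2.9 keeps participants withdrawn by the investigator on the same assessment schedule up to week 12 or frank psychosis. Anyone who progresses to first-episode psychosis counts as a treatment failure and from then on has safety assessments only.

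**The concern.** Under MAR, the chance that a value is missing may depend on observed values but, given those, not on the missing value itself. Exploring patterns means relating drop-out to what was observed, such as baseline and T1 scores. If drop-out is related to T1, MCAR is contradicted and MAR is not. If drop-out depends on the unseen T2 score beyond what baseline and T1 predict, the observed data hold no information on that dependence. The stated purpose of the exploration therefore cannot be met.

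The response has a matching gap. Multiple Imputation and MissForest, as usually run, predict missing values from observed ones and so rely on MAR. If evidence against MAR were somehow found, these methods would not address it.

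What is at stake is the primary result. The trial has one arm and its interest is the change over time. Bias in the T2 mean goes straight into that change, with no control arm to offset it. Section 2.9 creates one loss that is tied to outcome: a participant who progresses between T1 and T2 has no later severity score. One who progresses before T1 has no post-baseline severity score and, on the natural reading of the analysis-set rule, leaves the severity analysis altogether.

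**Working it through.** **1. The plan's own figures.** Section 2.8.2 gives no number. The setting comes from section 2.2: three visits, correlation r from 0.5 to 0.7, partial η² = 0.14, 20 participants, drop-out at most 20% (4 of 20). The stated sample sizes reproduce with the G*Power default, λ = f²·n·m·ε/(1 − r), f² = 0.14/0.86 = 0.163, m = 3, and the noncentral F with (m − 1)ε and (n − 1)(m − 1)ε degrees of freedom:

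- ε = 1: 12 (r = 0.5) to 8 (r = 0.7). Stated: 8–12.
- ε = 0.75: 14 to 10. Stated: 10–14.
- ε = 0.50: 19 to 12. Stated: 12–19.

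**2. What an exploration can show.** Simulated trials with n = 20, normal scores with SD 1, equal correlations, and 20% missing at T2. The assumptions, not taken from the documents, are a logistic drop-out model with slope 1 or 2 per SD, and a check in the form of a t-test at 5% comparing T1 scores of drop-outs and completers. Trials with fewer than two drop-outs (about 7%) were excluded. A negative bias makes T2 severity look too low, that is, too favourable.

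| Drop-out depends on | Slope | Check positive, r = 0.5 / 0.7 | Bias of T2 mean after MAR regression imputation (SD), r = 0.5 / 0.7 |
|---|---|---|---|
| Nothing (MCAR) | – | 5.4% / 5.1% | 0.00 / 0.00 |
| T1 score (MAR) | 1 | 34.2% / 34.2% | 0.01 / 0.01 |
| T1 score (MAR) | 2 | 73.0% / 72.1% | 0.01 / 0.01 |
| T2 score (MNAR) | 1 | 11.4% / 19.1% | −0.12 / −0.07 |
| T2 score (MNAR) | 2 | 20.6% / 37.2% | −0.18 / −0.12 |
| Part of T2 not predicted by baseline and T1 (MNAR) | 1 | 5.2% / 5.0% | −0.14 / −0.12 |
| Same | 2 | 5.5% / 5.4% | −0.20 / −0.17 |

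A separate run at r = 0.6 with 20–21% missing, counting trials with fewer than two drop-outs as negative, agrees:

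- MCAR: 4.7% positive.
- MAR, slopes 1, 1.5, 2: 33.0%, 54.3%, 69.6%.
- MNAR through T2, slope 1.5: 21.0%.
- MNAR through the unpredicted part, slopes 1, 1.5, 2: 4.9%, 4.5%, 4.8%, with large-sample bias −0.134, −0.174, −0.199 SD.

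A positive rate near 35% goes with almost no bias under MAR (slope 1) and with a bias of −0.12 SD under MNAR (slope 2, r = 0.7). A rate near 5% goes with no bias under MCAR and with −0.12 to −0.20 SD under the last mechanism. The result of the check does not tell these apart. A larger trial does not help: at n = 200 the check is positive in 68–100% of trials under MNAR through T2, in essentially all under MAR, and still in 4–5% under the last mechanism.

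**3. Size against the precision of the trial.** Standard error of the baseline-to-T2 change = √(2(1 − r)/n) = √(0.8/20) = 0.20 SD at r = 0.6. The bias range of 0.07 to 0.20 SD is 0.07/0.20 = 0.35 to 0.20/0.20 = 1.0 standard errors.

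**4. What drives that size.** The bias equals the fraction missing times d, the average distance in SD by which the unseen T2 values exceed their imputed values. With 4 of 20 missing, a bias of 0.20 means d = 1.0 and a bias of 0.07 means d = 0.35. One missing participant contributes d/20 = 0.05·d SD.

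**5. How many could be lost through progression.** The Introduction cites a 2-year transition risk of 16–19%. Assuming a constant hazard, 12 of 104 weeks gives 1 − 0.84^(12/104) = 2.0% to 1 − 0.81^(12/104) = 2.4%, or 0.4 to 0.5 of 20 participants. The 20% missing in step 2 is therefore the plan's drop-out ceiling from all causes, not the expected loss from progression.

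**The case against.** The best defence is that little missing data is expected. Section 2.9 tells participants who withdraw that they stop only treatment and continue visits, and it keeps investigator withdrawals on schedule. Progression to psychosis is recorded and classed as failure, so that loss is visible. The study is a 20-participant pilot, and section 2.8.1 promises an SAP before any data are summarised, which is the usual home for a delta analysis. The words on patterns may also cover drop-out reasons, which help to judge plausibility.

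Much of this stands. It limits the size of the problem, and the absence of a named MNAR analysis would not by itself be a finding. It does not rescue the stated rule. Drop-out reasons inform judgement but do not test MAR, and the text says what patterns can show and gets it wrong.

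Three stronger readings are tempting and are not supported.

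- A reader might infer that the check works in reverse, alarming when MAR holds and keeping quiet when it fails. The table shows a non-specific check: positive in about 5% of trials under MCAR, which is a case of MAR, and in 11–37% when drop-out depends on T2. It is uninformative throughout only if drop-out depends solely on the part of T2 that earlier scores do not predict.
- A reader might count every positive result under MAR as a false alarm. That presumes a primary model valid under MAR. The article offers mixed models only as a possible supplement and plans paired tests, which use participants with both scores. For such analyses, drop-out related to T1 is worth detecting and MAR-based imputation is a fair answer.
- A reader might point to withdrawal "if participation in the trial interferes with ongoing care or results in symptomatic worsening" as a source of unseen worsening. Those participants keep their scheduled assessments, so by plan this does not make T2 missing.

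**Conclusion.** The point holds as an error in stated text. Observed patterns can argue against MCAR but not against MAR, and the named response does not relax MAR. A clean exploration should not be reported as support for MAR.

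The practical size is modest. With 20% missing at T2 and slopes of 1 to 2 per SD, a MAR-based T2 mean is 0.07 to 0.20 SD too favourable, at most about one standard error of the change. The slopes, the t-test form of the check and the normal model are assumptions. So is the use of the full drop-out ceiling; with fewer missing values the bias shrinks in proportion. Loss after progression is the one route that the plan itself builds in. It probably involves few participants in 12 weeks, but their unseen scores may lie well above any imputed value, and the single-arm design passes that into the time effect. The correction is worth making because it is cheap and the article intends the results to support a larger study.

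**What to change.** Change section 2.8.2, or carry the change into the SAP, in two places.

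1. State that the exploration of missing-data patterns describes departures from MCAR, and is used to choose observed predictors of drop-out for a MAR-based analysis (mixed model or multiple imputation).
2. State that a sensitivity analysis to departures from MAR will be reported whatever the exploration shows. One example is delta-adjusted multiple imputation that shifts unobserved T2 CAARMS severity upward over a stated range, includes the values not collected after progression to psychosis, and reports where the conclusion changes.

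The cost is two sentences and one further analysis of data already collected. The downside is a reported range that may look less favourable than the primary estimate.

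### The two imputation methods named as the response to evidence against missing at random normally assume it, and MissForest used as a single imputation understates the standard error

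*Protocol article*

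**What the plan says.** Section 2.8.2 states the working assumption: "We expect withdrawn patients to be missing at random, and very few participants withdrawing consent". The analysis set is defined by "All patients having at least one post-baseline outcome measure will be included in each analysis". Next, "patterns of missing data will be explored to investigate any evidence against missing at random". The response to such evidence follows in the same sentence: "whose impact on the analysis will be considered by introducing imputation methods (i.e., Multiple Imputation or MissForest approach, depending on the missing data type". The parenthesis opens with i.e., so it reads as a complete list of two methods and not as examples.

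Section 2.8.1 gives the model that these data feed: "Our primary analysis will involve a generalized linear model with CAARMS psychotic symptom severity as the dependent measure and time as a repeated measure". Mixed models are a possible supplement, and paired baseline-to-endpoint tests are additional. Under section 2.9, participants who progress to first-episode psychosis leave the intervention and will "be classified as treatment failure, and only be assessed for safety outcomes until completing the 12-week follow-up period".

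**The concern.** The step is triggered by doubt about MAR, but the named methods in their usual form rest on MAR. An analysis that repeats the main analysis's assumption cannot measure what happens when the assumption fails.

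The design makes this relevant. The effect of interest is change over time in one arm, so losing the highest severity scores looks like improvement. Section 2.9 provides a route by which scores can be lost because of the outcome itself.

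MissForest raises a second problem. It returns one completed data set of predicted values. Analysed with ordinary standard errors, that data set contains too little variation and claims more information than was collected. The article names no step that carries the imputation uncertainty into the standard error. APS severity is the primary research endpoint, planned at a 5% type I error, so an inflated error rate would weaken the case for the larger trial that the Discussion foresees.

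**Working it through.** **Inputs from the article.** Section 2.2: N = 20; three visits (baseline, T1, T2); correlation r between visits 0.5 to 0.7; α = 5%; power 80%; partial η² = 0.14; dropout up to 20%, which is 0.20 × 20 = 4 people. Section 2.8.1: repeated-measures model as primary, paired tests as additional.

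**Assumptions not in the article.** Normal scores with unit SD and equal correlations; a stand-in for the MissForest software; for the MNAR runs only, a dropout slope of 1.5 per SD on the unseen T2 score, so that worse patients are more likely to leave.

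**Step 1: reproduce the plan's figures.** Within-subject F test with f² = 0.14/0.86 = 0.163, λ = f²·N·m·ε/(1 − r), df1 = (m − 1)ε, df2 = (N − 1)(m − 1)ε and m = 3. For example, N = 12, r = 0.5 and ε = 1 give λ = 0.1628 × 36/0.5 = 11.7. Required N for r = 0.5 and 0.7 is 12 and 8 (ε = 1), 14 and 10 (ε = 0.75), 19 and 12 (ε = 0.5). These match section 2.2 exactly. No sample-size figure is in dispute.

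**Step 2: why one deterministic fill is too narrow.** With equal correlations, predicting T2 from baseline and T1 has R² = 2r²/(1 + r), which is 0.333 (r = 0.5) or 0.576 (r = 0.7). The variance of a real change score is 2(1 − r), that is 1.0 or 0.6. For a filled-in change score it is R² + 1 − 2r, that is 0.333 or 0.176. With 4 of 20 filled:

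- r = 0.5: average variance 0.8 × 1.0 + 0.2 × 0.333 = 0.867; reported SE about √(0.867/20) = 0.208.
- r = 0.7: 0.8 × 0.6 + 0.2 × 0.176 = 0.515; reported SE about √(0.515/20) = 0.160.

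In simulation with a bagged-tree (random-forest type) imputer and data missing completely at random, the mean reported SE was 0.210 and 0.164. The actual spread of the estimate was 0.246 and 0.194. The ratios are 0.855 and 0.847.

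**Step 3: type I error with no true change.** Single regression prediction from baseline and T1, T2 values missing completely at random, r = 0.5–0.7, 20,000 trials per setting, several independent runs:

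| T2 values missing | Paired test, baseline to T2 | Three-visit time test (repeated-measures ANOVA in place of the primary model) |
|---|---|---|
| 4 of 20 | 9.2–9.9% | 8.4–8.9% |
| 2 of 20 | 6.9–7.3% | 6.4–6.6% |
| 1 of 20 | 5.5–5.8% across both tests | 5.5–5.7% |

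For reference, the 16 completers alone gave 4.8–5.2% on the paired test, and the three-visit test with nothing missing gave 5.2%. The bagged-tree imputer with 4 missing (3,000 runs per setting) gave 8.5–9.2% on the paired test under completely random or MAR missingness, with SEs 12–15% too small. Multiple Imputation with Rubin's rules gave 3.1–4.2%.

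**Step 4: what happens when MAR fails.** Paired baseline-to-T2 comparison, 4 missing, no true change, 3,000 runs per setting, assumed MNAR mechanism; negative bias means false improvement:

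| Method | Bias in SD, r = 0.5 / 0.7 | Type I error, r = 0.5 / 0.7 |
|---|---|---|
| Standard Multiple Imputation | −0.17 / −0.11 | 9.5% / 6.7% |
| Single forest-type imputation | −0.20 / −0.16 | 18.3% / 16.2% |
| Completers only | −0.12 / −0.07 | 8.6% / 7.1% |

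Neither planned method removes the bias. The sizes depend on the assumed slope.

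**Step 5: how often the section 2.9 route would operate.** The Introduction cites transition rates of about 16–19% at 2 years. If the hazard were constant (an assumption), the 12-week risk would be 1 − 0.84^(12/104) = 2.0% to 1 − 0.81^(12/104) = 2.4%, or 0.4 to 0.5 of 20 participants. The chance of at least one transition would be about 33–38%. A higher early hazard would raise these figures.

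**The case against.** **Multiple Imputation is a framework and can be run under MNAR.** This stands. A reader might infer that naming it commits the trial to MAR, and that goes too far: the remedy below is itself a form of Multiple Imputation. What remains is that the article names no MNAR variant in the sentence whose purpose is to address departures from MAR.

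**The SAP can settle the detail.** Section 2.8.1 has it approved before data are summarised, and pooling rules or delta steps may properly be left to it. But the article already fixes the pairing of trigger and response, and it lists single-imputation software as one of two responses. A SAP that follows it inherits both.

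**The choice may not be post hoc.** A reader might take the closing words about missing data type to mean that the method is picked after seeing the data. They may equally mean variable type, which is known in advance. The text does not decide this, and neither reading adds an MNAR method.

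**The inflation is modest at realistic dropout.** This largely stands. The highest rates use the 20% ceiling and a supplementary test. The article expects few withdrawals of consent and keeps people who stop treatment in follow-up. With one missing value the excess is under one percentage point.

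**Other information bears on MAR.** Reasons for withdrawal are sought and reported. They help, but they do not quantify the effect of a departure on the result.

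**Conclusion.** The point holds in two parts. First, the stated response to evidence against MAR consists of methods that, as standardly implemented, assume MAR, so it cannot show the effect of departures from it. Section 2.9 makes outcome-related missing data possible, although the expected number of transitions in 12 weeks is small. Second, MissForest used as one completed data set understates the standard error: type I error is about 8.5–10% with 4 of 20 T2 values missing, 6.5–7% with 2 and 5.5–6% with 1, against 5%. These figures rest on normal, equally correlated scores and on stand-ins for MissForest.

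A reader might also infer that the sensitivity analysis is bound to agree with the primary result whatever the mechanism. That is not shown. The type I figures in Step 3 come from data missing completely at random, the MNAR figures rest on one assumed dropout slope, and a method that rejects too often need not agree with the primary analysis. The supportable statement is that the planned methods do not test the assumption. Severity is minor to moderate: the step is conditional, and the trial is a 20-person, single-arm pilot.

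**What to change.** 1. Keep a likelihood-based mixed model on all observed scores as the MAR analysis. Section 2.8.1 already allows mixed models.
2. Pre-specify the sensitivity analysis as a delta-adjusted Multiple Imputation pooled with Rubin's rules: shift the imputed T2 scores towards greater severity in fixed steps, and report the shift at which the conclusion changes (the tipping point).
3. Run it whatever the exploration of missing-data patterns shows. With at most a handful of missing values among 20 people, finding no evidence against MAR is weak support for it.
4. Do not use single MissForest imputation for outcome data, or use it only inside a multiple-imputation scheme with pooled variance.
5. Say whether missing data type means variable type or missingness mechanism.

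The cost is a few sentences in the SAP and a short extra analysis. The downside is wider intervals. Sample size and visit schedule do not change.
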